#### 2.5.5. Data Management and Confidentiality

Data will be entered into a secured electronic database accessible only to the research team. All patient identifiers will be removed and replaced with unique study codes. The database will be password-protected and stored on encrypted institutional servers.

#### 2.5.6. Statistical Analysis

All statistical analyses will be performed using appropriate parametric or non-parametric tests, depending on data distribution as assessed by the Shapiro–Wilk test. Descriptive statistics will be used to summarize baseline demographic, clinical, and laboratory characteristics, with results expressed as mean ± standard deviation (SD) or median (interquartile range, IQR) for continuous variables, and as absolute and relative frequencies for categorical variables. Associations between biomarker concentrations and clinical severity scores (SOFA, DECAF, Ottawa COPD Risk Scale, BAP-65, and CFS) will be evaluated using correlation coefficients (Pearson or Spearman, as appropriate). Due to the high heterogeneity of patients with AECOPD in the ED, multivariable analyses will be performed to account for potential confounding factors. Regression models will be adjusted for specific clinical covariates, including demographic characteristics, relevant comorbidities, baseline disease severity indicators, and validated clinical severity scores (SOFA, DECAF, BAP-65, Ottawa COPD Risk Scale, and Clinical Frailty Scale). The number of predictors included in multivariable models will be limited in relation to the number of observed outcome events (approximately 5–10 events per predictor when possible). Effect sizes and confidence intervals will be reported alongside *p*-values to facilitate appropriate interpretation of results. Receiver Operating Characteristic (ROC) curve analysis will be applied to determine the discriminative performance of individual biomarkers, and the area under the curve (AUC) will be calculated to identify optimal cutoff values associated with adverse outcomes. Short-term prognosis will be further analyzed through Kaplan–Meier survival curves and log-rank tests for 28-day mortality. A two-tailed *p*-value < 0.05 will be considered statistically significant for all analyses.

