## Abstract

**Background/Objectives**: Chronic obstructive pulmonary disease (COPD) remains a major global health problem, affecting over 300 million people worldwide. Its high morbidity and mortality rates impose substantial psychosocial and financial burdens on patients and healthcare systems. In the emergency setting, managing acute exacerbations of COPD (AECOPD) poses a major clinical challenge, as these patients often present with multi-organ dysfunction secondary to hypoxia and hypercapnia. Identifying reliable prognostic biomarkers could improve early risk stratification, guide therapeutic decisions, and enhance patient outcomes. **Methods**: This multicenter, prospective, observational study aims to evaluate the prognostic significance of several novel biomarkers—resistin, club cell secretory protein 16 (CC16), interleukin-6 (IL-6), tumor necrosis factor-alpha (TNF-α), S100β protein—alongside conventional markers such as N-terminal-pro–B-type-Natriuretic-Peptide (NT-proBNP), D-dimer, high-sensitivity troponin I (hs-cTnI), C-reactive protein (CRP), and procalcitonin in patients with AECOPD admitted to the Emergency Department (ED). Blood samples will be collected at admission. The novel biomarkers (resistin, CC16, IL-6, TNF-α, S100β) will be measured using standardized ELISA kits, while conventional biomarkers (NT-proBNP, troponin I, CRP, procalcitonin) will be analyzed using routine automated clinical laboratory methods. Correlations between biomarker levels, clinical and imaging data, severity scores (GCS, SOFA, CFS, Ottawa COPD Risk Scale, DECAF, BAP-65), and short-term outcomes (hospital discharge status and 28-day survival) will be assessed. The study has received approval from the Ethics Committee of the “Iuliu-Hatieganu” University of Medicine and Pharmacy, Cluj-Napoca, and all participating hospitals. Written informed consent will be obtained from all participants or their legal representatives. **Results:** This study protocol does not report results, as data collection and analysis are ongoing. **Conclusions /Expected Impact:** By identifying novel biomarkers with prognostic and pathophysiological relevance, this research aims to inform the development of early risk stratification tools and support future evidence-based approaches to the management of critically ill COPD patients in the ED.

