### 2.3. Sample Size and Study Duration

The study is planned to include approximately 100 consecutive eligible patients admitted over a 15-month period. The sample size was estimated based on local patient volumes and previous annual ED statistics (over 600 COPD admissions per year), ensuring sufficient statistical power to detect correlations between biomarker levels and clinical outcomes. Baseline biomarker values will be analyzed exclusively for prognostic correlation with the later need for oxygen therapy, NIV or IMV, and will not be used to guide acute therapeutic escalation or de-escalation.

Based on an estimated annual number of approximately 600 COPD presentations to the ED, we anticipated enrolling around 100 eligible patients meeting the study inclusion criteria. In these participants, five biomarkers (resistin, CC16, IL-6, TNF-α, and S100β protein) will be measured and correlated with disease severity and short-term outcomes.

A post hoc power analysis performed using G*Power software (version 3.1.9.7) for a two-tailed Mann–Whitney test, assuming a large effect size (Cohen’s d = 0.8) and a Bonferroni-adjusted significance level (α = 0.01), indicated a statistical power (1 − β) of approximately 0.91–0.92. This suggests that a sample size of 100 participants could be adequate for detecting large and clinically relevant differences in biomarker levels between well-defined severity or outcome groups. In patients with acute exacerbations of COPD, Vassiliou et al. reported higher serum resistin levels during the acute phase as compared to the stable phase after clinical recovery (median at admission 19.44 ng/mL vs. 9.70 ng/mL at follow-up), indicating a large difference between clinically distinct states [4]. We will reevaluate the sample size after enrollment of 20 patients, and we plan to extend the study to other centers, if necessary.

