#### 2.5.4. Data Monitoring

At ED admission, all patients will undergo assessment using validated severity and prognostic scores available on the MDCalc platform (www.mdcalc.com). The following tools will be applied: mMRC Dyspnea Scale for grading dyspnea severity, the SOFA score, GCS, for evaluating neurological impairment secondary to hypoxia or hypercapnia, and the CFS, adapted for triage levels used in Romania, to estimate frailty and predict mortality. Additional prognostic scores specific to COPD will be applied, including the Ottawa COPD Risk Scale (predicting 30-day mortality or severe adverse events such as myocardial infarction or the need for intubation), the DECAF Score for in-hospital mortality in acute exacerbations of COPD, and the BAP-65 Score for in-hospital mortality prediction.

Serum biomarker levels will be measured according to the previously described analytical protocol. Based on clinical status and therapeutic requirements, study participants will be classified into three groups: COPD patients requiring supplemental oxygen therapy, those requiring NIV, and those requiring IMV. These measurements are intended solely to establish prognostic associations with subsequent respiratory support requirements and will not influence real-time clinical management.

At discharge from the ED or before hospitalization in the Pulmonology Department or the Internal Medicine Department, patient outcomes will be documented as improved (reduction in dyspnea and clinical instability, no requirement for escalation of respiratory support, decreased level of respiratory support, and evidence of improving gas exchange), stable (no significant improvement but no deterioration, with the same level of respiratory support maintained), worsened (increased respiratory distress, need for escalation of respiratory support, and worsening gas exchange or hemodynamics), or deceased (ED mortality). The total duration of hospitalization will be recorded, as well as survival time, including the date of death if it occurred during the ED stay or hospitalization. Early survival will additionally be assessed at 28 days through telephone follow-up.

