## Figures and Tables

**Table 1 diagnostics-16-00122-t001:** Objectives proposed by the research team.

Primary Objective	Secondary Objectives
To evaluate the association between serum levels of resistin, CC16, IL-6, TNF-α, and S100β measured at ED admission and early outcomes, including discharge status and 28-day survival, in patients presenting with acute exacerbations of COPD (AECOPD).	To determine biomarker cutoff values associated with the need for escalation of respiratory support (oxygen therapy, non-invasive ventilation, or invasive mechanical ventilation).
	To identify combinations of circulating biomarkers and established clinical scores that best predict short-term mortality and organ dysfunction.
	To assess the relationship between diaphragmatic contractility evaluated by bedside ultrasound and circulating biomarker levels, in relation to the level and duration of ventilatory support.
	To explore the potential role of biomarker-based risk stratification in informing clinical decision-making for AECOPD patients in the ED.

Legend: CC16—club cell secretory protein 16; IL-6—interleukin-6; TNF-α—tumor necrosis factor-alpha; S100β—S100 calcium-binding protein beta; ED—Emergency Department; COPD—chronic obstructive pulmonary disease; AECOPD—acute exacerbation of chronic obstructive pulmonary disease.

**Table 2 diagnostics-16-00122-t002:** Inclusion criteria for eligible study participants.

Inclusion Criteria	
Age ≥ 50 years. Confirmed prior diagnosis of COPD, regardless of disease stage or ongoing therapy:	
(a) the GOLD spirometric grades	GOLD I (FEV_1_ ≥ 80%) GOLD II (50% ≤ FEV_1_ < 80%) GOLD III (30% ≤ FEV_1_ < 50%) GOLD IV (FEV_1_ < 30%)
(b) ABE category assessment	A—low symptom burden and low risk of exacerbations; 0–1 moderate exacerbations in the previous year, with no hospitalizations B—increased symptoms but low risk of exacerbations; 0–1 moderate exacerbations in the previous year, without hospitalization E—high exacerbation risk, defined as ≥ 2 moderate exacerbations or ≥1 exacerbation requiring hospitalization in the previous year, irrespective of the level of symptoms
Admission to the ED with acute exacerbation of COPD. Signed informed consent obtained from the patient or legal representative.	

Legend: COPD—chronic obstructive pulmonary disease; GOLD—Global Initiative for Chronic Obstructive Lung Disease; FEV_1_—forced expiratory volume in 1 s; ED—Emergency Department.

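### No method assigned to outcomes uses the order of the four-level status scale or of the respiratory support level; naming an ordered analysis would gain power at N = 100 for a change of wording

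*Protocol article*

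**What the plan says.** Table 1 sets the primary objective as the association of five admission biomarkers with "early outcomes, including discharge status and 28-day survival". The Abstract words the outcome as "short-term outcomes (hospital discharge status and 28-day survival".

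Section 2.5.4 says that, on leaving the ED or before ward admission, "patient outcomes will be documented as improved", stable, worsened "or deceased (ED mortality". The levels are defined by direction of clinical change, so they have a natural order. The same section classifies patients by oxygen, NIV or IMV, which is also ordered.

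The methods tied to outcomes are:
- Section 2.3: power for "for a two-tailed Mann–Whitney test", with d = 0.8, alpha = 0.01 and a result of about 0.91–0.92, for "approximately 100 consecutive eligible patients admitted over a 15-month period".
- Section 2.5.6: ROC curves with cutoffs for adverse outcomes, and Kaplan–Meier curves with log-rank tests for 28-day mortality.
- Section 2.5.6, on regression: "The number of predictors included in multivariable models will be limited in relation to the number of observed outcome events", at roughly 5–10 events per predictor.

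Pearson or Spearman correlation is named in section 2.5.6 for severity scores. The model type of the regressions is not given.

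**The concern.** A two-group test, a ROC curve and an events-per-predictor rule all work on a two-class outcome. Section 2.5.4 contains no such outcome for status or support level. If the analysis follows the tools that are named, the four levels will be collapsed, most naturally to worsened or deceased against the rest. That merges improved with stable and leaves a small second group. If the general provision for suitable parametric or non-parametric tests is used instead, the usual choice for four groups is Kruskal–Wallis, which ignores the order.

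At stake is power on an outcome in the primary objective, in a study of about 100 patients with five biomarkers tested at 0.01 each. Adjustment is at stake too. With an assumed 15–25 events, the article's own rule allows between 15/10 = 1.5 and 25/5 = 5 predictors, while section 2.5.6 lists five severity scores besides demographics, comorbidities and disease severity.

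**Working it through.** **Inputs from section 2.3.** N = 100, d = 0.8, two-sided alpha = 0.01, stated power 0.91–0.92.

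**Assumed, because the article gives no outcome distribution.** The mixes of improved/stable/worsened/deceased below, the cut at worsened or deceased, and one common odds ratio across levels.

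**1. The stated figure.** Normal formula: power = Φ(d·√(N·v) − 2.576), where v = q(1 − q) and q is the share in the smaller group. At 50:50, v = 0.25, so Φ(0.8 × 5 − 2.576) = Φ(1.424) = 0.923. The noncentral t gives 0.912, and the Mann–Whitney efficiency factor 3/π gives 0.897. The stated figure therefore matches groups of about equal size.

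**2. A two-group split with a small second group.** Same formula:
- 25:75: Φ(0.8 × √18.75 − 2.576) = 0.81
- 20:80: Φ(0.8 × 4 − 2.576) = 0.73
- 15:85: Φ(0.8 × √12.75 − 2.576) = 0.61

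With the 3/π factor these become 0.77, 0.69 and 0.57.

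**3. Information in the ordered scale.** Under proportional odds, the information per patient is proportional to 1 − Σp³ (Whitehead). For two groups this equals 3q(1 − q), so the two are on one scale.
- 60/25/12/3: 0.767 against 0.383, ratio 2.0
- 50/30/15/5: 0.844 against 0.480, ratio 1.8
- 40/35/20/5: 0.885 against 0.562, ratio 1.6

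Putting v = (1 − Σp³)/3 and a log odds ratio of 0.8 per SD into the formula gives ordered power of 0.93, 0.95 and 0.96.

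**4. Simulation.** N = 100, alpha 0.01, 6,000 runs per mix. The slope is 0.85 per SD, which gives d of 0.80–0.82 at the worsened/deceased cut.

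| Mix (%) | Two-group Mann–Whitney | Kruskal–Wallis | Ordered (Spearman) |
|---|---|---|---|
| 60/25/12/3 | 0.54 | 0.75 | 0.89 |
| 50/30/15/5 | 0.67 | 0.81 | 0.93 |
| 40/35/20/5 | 0.76 | 0.84 | 0.94 |
| 70/15/10/5 | 0.55 | 0.65 | 0.83 |
| 80/10/7/3 | 0.38 | 0.46 | 0.69 |

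Repeat runs differ by about 0.01. The ordered test is ahead in every mix. It comes within about two points of 0.91 or better only in the first three.

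**5. At alpha 0.05.** Section 2.5.6 applies 0.05 to all analyses, while the power statement uses 0.01. With 1.960 in place of 2.576, the formula gives for 60/25/12/3 Φ(2.857 − 1.960) = 0.82 for the split and Φ(4.044 − 1.960) = 0.98 for the ordered analysis. The gain is smaller but has the same direction.

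No power was computed for the three-level support scale. The reasoning is the same, but its size would depend on the mix.

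**The case against.** The strongest reply is that the article never commits to a split. Section 2.5.6 allows suitable tests in general, leaves the regression type open and names Spearman. The Abstract and section 2.3 both speak of correlating biomarkers with outcomes. A rank correlation with the status scale would fit the text, and the exact model may sit in a fuller plan. This stands in part. A reader might infer that every named method forces the scale into two, and the document does not support that. What remains is narrower: where the article does attach a method to an outcome, the method is two-class or event-based, and correlation coefficients are attached only to severity scores.

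Second, section 2.5.4 does not call its four levels discharge status. It records them at ED discharge or before ward admission and counts ED deaths, whereas the Abstract refers to hospital discharge. Linking the scale to the primary objective is an inference. This stands and must be settled first.

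Third, ROC curves suit the cutoff objective in Table 1, and log-rank tests suit 28-day mortality. This also stands: neither is misapplied, and both can stay.

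Fourth, the simulations make proportional odds exactly true, which favours the ordered test. That is fair, and is why the binary cuts should be reported alongside.

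**Conclusion.** The point holds as an inexpensive improvement to the analysis. With an assumed 15–25% worsened or deceased and at most 60% improved, an ordered analysis has power of about 0.89–0.94. A two-group split has about 0.55–0.75 and Kruskal–Wallis about 0.75–0.85. These figures rest on N = 100, alpha 0.01, d of about 0.8, proportional odds, no covariates, and a cut that the plan does not state.

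Two stronger readings are not supported. One is that an ordered analysis always brings back the stated 0.91–0.92. It does not: with 70% or 80% improved it gives about 0.83 or 0.70, though still well above the split at 0.55 or 0.37. It does nothing for 28-day survival. The other is that the ordinal effective sample size (77–88) can be set against 15–25 events to justify many more adjusters. Those are different measures. On one scale the comparison is 77–88 against 38–56, a gain of about 1.6–2.0 times, so adjustment should stay modest.

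That the stated power needs near-equal groups is a separate sample-size matter and is used here only as the reference figure.

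**What to change.** 1. Define discharge status once, stating its levels and time point, and reconcile the Abstract (hospital discharge) with section 2.5.4 (ED discharge or before ward admission).
2. In section 2.5.6, name proportional-odds regression on the ordered levels as the primary analysis of each biomarker against discharge status, reporting one common odds ratio with its confidence interval. Give a Spearman or trend test as the unadjusted version.
3. Use the same approach for respiratory support level (oxygen, NIV, IMV).
4. Keep ROC curves and binary cuts as secondary analyses, and report the odds ratio at each cut as a check of proportionality. Leave log-rank for 28-day mortality.
5. Keep the number of adjusters small and fixed in advance.
6. Show power over a range of outcome mixes. The sample-size review after 20 patients in section 2.3 is a natural point to look at the observed mix, without looking at its relation to the biomarkers.

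The cost is wording: no added patients, samples or visits. The downside is reliance on the proportional-odds assumption, which item 4 makes visible.

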In parallel, S100β may index hypoxic neuro-injury during severe exacerbations. Elevated serum S100β has been linked to cerebral ischemic stress and neuronal damage in acute respiratory and critical illnesses, supporting its potential role as a neuro-systemic prognostic adjunct in the ED [16,17,22,23].

Originality and downstream impact:

To our knowledge, no ED based study has jointly evaluated the prognostic value of resistin, CC16, IL-6, TNF-α, and S100β in patients with AECOPD. Prior studies have assessed these molecules individually or in non-acute contexts, but none have integrated them within a unified, outcome-oriented framework [4,5,6,7,8,9,10,11,12,13,14]. Our study addresses this gap and is designed to derive cut-off thresholds and a parsimonious composite prognostic score applicable to emergency workflows.

If confirmed, these findings will support biomarker-guided algorithms—for instance, thresholds triggering NIV/IMV escalation or identifying extubation readiness when combined with diaphragmatic ultrasound—and may inform future therapeutic trials aimed at modulating inflammatory and epithelial-repair pathways (e.g., anti-TNF agents or CC16-protective interventions).

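### ROC-optimal cut-offs and the composite score come from one cohort of about 100 patients with no optimism correction described; the Kaplan–Meier groups, the adjusters kept and the test of added value are left open

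*Protocol article*

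**What the plan says.** All of this concerns the protocol article.

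- **Cohort.** Section 2.3 plans "approximately 100 consecutive eligible patients admitted over a 15-month period". It adds: "We will reevaluate the sample size after enrollment of 20 patients". No rule for an increase is given.
- **Cut-offs.** Section 2.5.6 applies ROC analysis to individual biomarkers, and "the area under the curve (AUC) will be calculated to identify optimal cutoff values associated with adverse outcomes". Table 1 links cut-offs to escalation of respiratory support; the Introduction speaks of thresholds for both mortality and ventilator escalation.
- **Survival.** Section 2.5.6 then names "Kaplan–Meier survival curves and log-rank tests for 28-day mortality" and does not define the groups to be compared. The significance level is 0.05 throughout.
- **Composite score.** Section 3 states that the study "is designed to derive cut-off thresholds and a parsimonious composite prognostic score applicable to emergency workflows". It expects better discrimination and calibration than DECAF, the Ottawa scale and BAP-65 alone.
- **Adjustment.** The regression models are to adjust for demographics, comorbidities, baseline severity indicators and "validated clinical severity scores (SOFA, DECAF, BAP-65, Ottawa COPD Risk Scale, and Clinical Frailty Scale". The next sentence limits the number of predictors by the number of events: "approximately 5–10 events per predictor when possible".

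**The concern.** A cut-off chosen because it separates outcomes best in a sample will look better in that sample than in new patients. The same is true of a score whose weights are fitted there. With 100 patients and perhaps 10–20 deaths the difference is large. If the same split then defines the survival groups, the log-rank test ignores the search over cut-offs and its p-value is too small.

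Two further gaps make this worse. The covariate list is far longer than the events rule can admit for mortality, and nothing says which covariates stay, so the choice may be made after the data are seen. And the headline expectation, that biomarkers improve on existing clinical scores, has no matching discrimination or calibration analysis.

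Thresholds and a composite score are what the study says it is designed to produce, and section 3 foresees their use in decisions on ventilatory support if confirmed.

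**Working it through.** **Plan's own figure.** Section 2.3 gives power 0.91–0.92 for 100 patients, "assuming a large effect size (Cohen’s d = 0.8" and two-sided alpha 0.01. With 50 per group, the normal approximation is Φ(0.8 × √(50/2) − 2.576) = Φ(4.000 − 2.576) = Φ(1.424) = 0.923; the noncentral t gives 0.912. The figure reproduces for an equal split. It concerns a two-group comparison and says nothing about the accuracy of cut-offs or of a fitted score.

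**Assumptions.** The article gives no mortality; 8–30 deaths per 100 were examined, mainly 10–20. It names no cut-off criterion; the Youden index was assumed, searched over all cuts in either direction.

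**Log-rank at a same-data cut-off.** Biomarkers unrelated to outcome, N = 100, exponential death times censored at day 28, test at 0.05:

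| How the groups are formed | False-positive rate per biomarker |
|---|---|
| Cut optimised on 28-day death | 36–37% (10 and 20 deaths); 36–38% in a second simulation (8–30 deaths) |
| Cut optimised on a 30% escalation outcome that includes all deaths | about 12–21% (10–20 deaths) |
| Median split | about 5% |

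A repeat of the escalation scenario (8,000 runs per setting) gave 12–22% with fixed counts and 13–24% with random counts, so that range is approximate. With five independent biomarkers cut on death, at least one was significant in 89–91% of studies, against 22–23% with median splits. If the direction of each biomarker is fixed in advance, the repeat gave about 21% instead of 36–37% for a cut optimised on death.

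**Composite score.** A logistic model of five noise biomarkers, judged on the patients it was fitted to (true AUC 0.50), and the same five added to one informative score (true AUC about 0.75):

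| Event rate | Apparent AUC, five noise biomarkers | Apparent AUC gain over score | Gain in new patients |
|---|---|---|---|
| 10% | 0.70 | +0.070 | −0.063 |
| 20% | 0.66 | +0.043 | −0.040 |
| 30% | 0.63 | +0.033 | −0.032 |

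**Events rule.** Predictors allowed = events ÷ 10 to events ÷ 5.

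- 10 deaths: 1 to 2. 15 deaths: 1 to 3. 20 deaths: 2 to 4.
- Five scores plus one biomarker is 6 predictors: 6 × 5 = 30 to 6 × 10 = 60 events.
- Adding age, sex, one comorbidity and one severity indicator makes 10 predictors: 50 to 100 events, out of 100 patients.

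**Added value.** Section 3 expects a gain in discrimination and calibration over three named scores. Section 2.5.6 plans ROC for individual biomarkers only, names no calibration measure, and does not compare a score with the score plus biomarkers.

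**The case against.** The strongest case on the other side has five parts.

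- **Log-rank groups.** A reader might infer that the log-rank p-values are invalid as planned. The text does not support that. It never says that the curves are split at ROC cut-offs, or by biomarker at all. Other groupings appear in the article: oxygen, NIV and IMV in section 2.5.4, and Rome severity in section 2.2. Nor does it say that the cut is optimised on death. The inflation is therefore conditional. ROC cut-offs remain the likely reading, because they are the only biomarker cut-offs mentioned.
- **Adjusters.** A reader might also infer that the plan commits to more adjusters than its rule allows. It does not: it says that the number will be limited, so the list is a candidate pool. With 30 or more events, as escalation may provide, five scores plus one biomarker meet the lower limit. What stands is the missing priority order and a cap that applies only when possible.
- **Score simulations.** At 10–20 events, a six-predictor model breaks the plan's cap, so those rows show the cost of exceeding it. The 30% row just meets the lower limit and still shows a false gain of 0.033.
- **Added value.** Regression adjusted for the clinical scores gives some evidence of it. It is not a measure of incremental discrimination or calibration.
- **Condensed article.** An unseen analysis plan may contain internal validation. This is a fair limit on the optimism point, since silence in an article is weak evidence. It does not settle the covariate list against the cap, or the mismatch between sections 2.5.6 and 3.

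**Conclusion.** The point holds in a conditional form. Apparent AUCs, cut-off performance and the composite score will be too favourable if reported as described: five uninformative biomarkers would show an AUC of about 0.66–0.70 at 10–20% mortality. If Kaplan–Meier groups use ROC cut-offs, the log-rank error rate for a noise biomarker is about 36–37% when the cut is optimised on death. It is lower, about 12–21% in the one scenario tried, when the cut is optimised on escalation. At 10–20 deaths only 1–4 predictors fit the plan's rule, and the article does not say which.

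It would go too far to conclude that uninformative biomarkers will in general look prognostic. A test of a single biomarker's full AUC keeps about 5% error; the inflation arises at the optimised cut and in the apparent performance of a fitted score.

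The figures rest on assumed event rates, the Youden criterion and independent biomarkers. Correlation would lower the any-of-five figures but not those per biomarker.

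**What to change.** 1. State how the Kaplan–Meier groups are formed, using pre-set groups such as the median or tertiles, and test each biomarker as a continuous variable.
2. Name the cut-off criterion and the outcome it is optimised on. Report bootstrap optimism-corrected AUC, calibration and intervals for the cut-offs, repeating cut-off and variable selection in every resample.
3. Name in advance a short, ranked list of adjusters under a firm cap. For mortality, put one clinical score first.
4. Compare score plus biomarker with score alone, by likelihood ratio and by corrected AUC.
5. Label the thresholds and composite score hypothesis-generating until confirmed in other patients.

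The cost is wording, slightly more programming, lower reported AUCs and fewer covariates adjusted for. No new data are needed.

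### The log-rank test, the only method tied by name to 28-day mortality, would need each biomarker cut into groups, losing information on which the Mann–Whitney power figure relies; a continuous-biomarker model avoids this loss

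*Protocol article*

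**What the plan says.** Table 1 makes the primary objective the association of five biomarkers measured at ED admission with "early outcomes, including discharge status and 28-day survival".

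Section 2.3 supports 100 patients with a power calculation for a "two-tailed Mann–Whitney test, assuming a large effect size" of d = 0.8, at a Bonferroni-adjusted alpha of 0.01. It reports that this "indicated a statistical power (1 − β) of approximately 0.91–0.92" and concludes that "a sample size of 100 participants could be adequate for detecting large and clinically relevant differences in biomarker levels". It gives no group sizes, mortality, number of deaths or hazard ratio.

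Section 2.5.6 does not name the Mann–Whitney test. It plans:
- parametric or non-parametric tests chosen by data distribution;
- correlations with severity scores;
- multivariable regression, with the number of predictors limited by the number of events;
- ROC analysis of individual biomarkers for adverse outcomes.

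On 28-day mortality it then says: "Short-term prognosis will be further analyzed through Kaplan–Meier survival curves and log-rank tests for 28-day mortality". No other method in the section is attached to that outcome by name. The section closes with a two-sided 0.05 threshold for all analyses.

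**The concern.** The powered test and the named survival test use the biomarker differently. A Mann–Whitney test compares its full distribution between two outcome groups. A log-rank test compares survival between groups of patients, so to test a biomarker it must first be cut. Cutting discards the ordering of patients within each group, and power falls even with the same patients, effect size and alpha.

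At stake is how a non-significant 28-day result is read. A reader who sees a power above 0.90 in section 2.3 may take a null log-rank test as evidence that a biomarker has no prognostic value, although the test could have had much less power than that.

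**Working it through.** **Inputs from the article.** N = 100, d = 0.8, two-sided alpha 0.01 and stated power 0.91–0.92 (section 2.3); alpha 0.05 (section 2.5.6).

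**Assumptions, not in the article.** Two groups of 50 for the stated power. For the survival test: a normally distributed biomarker (after transformation) shifted by 0.8 SD in patients who die, death times uniform over 28 days, a split at the pooled median, and 10 to 50 deaths.

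**Step 1: reproduce the stated power.** The noncentrality is δ = d·√(m₁m₂/(m₁+m₂)), with m = n × the relative efficiency of the test.
- Efficiency 1: δ = 0.8 × √25 = 4.00. Power is 0.913 (noncentral t) or 0.923 (normal approximation).
- Efficiency 3/π (Mann–Whitney, normal data): m = 50 × 0.955 = 47.7, δ = 0.8 × √23.87 = 3.91. Power is 0.897 (noncentral t) or 0.909 (normal approximation).

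The printed figure therefore matches a comparison of an uncut biomarker between two roughly equal groups.

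**Step 2: cost of a median split in the same 50:50 case.** The efficiency of a median split is 2/π = 0.637, so m = 31.8 and δ = 0.8 × √15.9 = 3.19. Power is 0.70 at alpha 0.01 and 0.88 at alpha 0.05.

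Two cross-checks at alpha 0.01: with 50 deaths the risks above and below the median are 0.655 and 0.345, which gives 0.71 by two proportions. The implied hazard ratio, ln(0.345)/ln(0.655) = 2.52, gives 0.76 by the Schoenfeld formula.

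**Step 3: vary the number of deaths.** Log-rank (median split) and the Cox score test (continuous biomarker) were simulated with 20,000 cohorts per row. Mann–Whitney is by the noncentral t with efficiency 3/π.

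| Deaths of 100 | Log-rank, 0.01 | Cox, 0.01 | Mann–Whitney, 0.01 | Log-rank, 0.05 | Cox, 0.05 | Mann–Whitney, 0.05 |
|---|---|---|---|---|---|---|
| 50 | 0.70 | 0.89 | 0.90 | 0.87 | 0.97 | 0.97 |
| 30 | 0.60 | 0.84 | 0.83 | 0.82 | 0.95 | 0.94 |
| 20 | 0.39 | 0.71 | 0.69 | 0.71 | 0.89 | 0.87 |
| 15 | 0.25 | 0.60 | 0.57 | 0.57 | 0.81 | 0.79 |
| 10 | 0.27 | 0.41 | 0.39 | 0.54 | 0.66 | 0.64 |

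Separate runs agree within about three points; for 20 deaths at alpha 0.01 they gave 0.36–0.39 for log-rank and 0.69–0.72 for Cox. The log-rank figures are uneven with few deaths because the test statistic is discrete. Under the null with 20 deaths and nominal 0.01, rejection rates were 0.008 (log-rank), 0.0095 (Cox) and 0.008 (Mann–Whitney).

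**Step 4: separate the two causes, 20 deaths at alpha 0.01.** Going from 50 to 20 deaths lowers Mann–Whitney power from 0.90 to 0.69, which is unequal group size and affects any test. Replacing the continuous Cox term by a median split lowers power further, from 0.71 to 0.39. Only this second drop is due to grouping.

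**Step 5: other cut points.** With 20 deaths at alpha 0.01, log-rank power is 0.50 for a cut at either the upper tertile or the upper quartile. With 10 deaths, an upper-quartile cut gives 0.40 against 0.41 for Cox. The size of the loss therefore depends on a grouping rule that the article does not give. Type I error was not checked for these other cuts.

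**The case against.** Several points stand on the other side.

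- **The log-rank test is not declared the main test.** It is introduced as a further analysis, after ROC analysis and event-limited regression. The empirical AUC is the Mann–Whitney statistic divided by n₁n₂, so an uncut analysis equivalent to the powered one may already be planned for outcomes, and the regression may use continuous biomarkers. This stands. The article does not, however, tie any of these to 28-day mortality.
- **Grouping by biomarker is an inference.** The sentence does not say what is compared, and the three respiratory-support groups in section 2.5.4 could also be meant. This stands, so the point is conditional on the log-rank test being used for the biomarkers, as the primary objective suggests.
- **Section 2.3 claims no power for a survival test.** It limits itself to biomarker differences between groups. This stands: the printed figure is not an error.
- **Model type and coding are often left to an analysis plan.** This is true, and their absence is not the complaint. The point concerns the method that the article does name.

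A reader might infer that the log-rank test has 0.70 power on the protocol's own inputs and so misses a large effect about three times as often as stated (30% against 8–9%). The article does not support that. The 0.70 needs 50% mortality by day 28, a median split and alpha 0.01, and only the alpha is in the text. At the 0.05 of section 2.5.6, the same 50-death case gives 0.87–0.88, a miss rate of 12–13%.

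**Conclusion.** The point holds as an inexpensive improvement in method, not as a wrong figure. The one method tied by name to 28-day mortality would, if applied to the biomarkers, discard information that the section 2.3 power calculation counts on.

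Under a median split, N = 100 and d = 0.8, the loss against a continuous Cox term with 15 to 50 assumed deaths is about 20 to 35 points of power at alpha 0.01 and about 10 to 24 points at alpha 0.05. Other cut points can make it smaller. These ranges rest on assumed death counts, a normal biomarker and uniform death times.

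A continuous term removes this loss only. With 20 deaths its power at alpha 0.01 is still about 0.70, so it does not restore 0.91 when deaths are few. The conflict between alpha 0.01 and 0.05 is a separate matter and needs its own resolution.

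**What to change.** **Section 2.5.6.** Name as the main 28-day analysis a Cox model, or logistic regression for death by day 28, with each of the five biomarkers entered as a continuous, log-transformed term. Report the hazard or odds ratio per SD with its confidence interval. Keep the Kaplan–Meier curves and log-rank tests as descriptive displays.

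**Section 2.3.** State that 0.91–0.92 applies to a comparison of the continuous biomarker between two groups of roughly equal size at alpha 0.01, and not to the log-rank test. Do not print 0.70 as the protocol's log-rank power; any survival power should state its assumed deaths and grouping rule and be given as a range.

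**Cost.** A few sentences and one extra model per biomarker. The continuous term assumes log-linearity, which can be checked on the same data. A Cox model uses the same death times as the Kaplan–Meier curves, and logistic regression needs only 28-day status. No extra patients, samples or procedures are required.
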